## Abstract

**Background:**

Our previous randomized double-blind study showed that drinking hydrogen (H_2_) water for 48 weeks significantly improved the total Unified Parkinson’s Disease Rating Scale (UPDRS) score of Parkinson’s disease (PD) patients treated with levodopa. We aim to confirm this result using a randomized double-blind placebo-controlled multi-center trial.

**Methods:**

Changes in the total UPDRS scores from baseline to the 8^th^, 24^th^, 48^th^, and 72^nd^ weeks, and after the 8^th^ week, will be evaluated. The primary endpoint of the efficacy of this treatment in PD is the change in the total UPDRS score from baseline to the 72^nd^ week. The changes in UPDRS part II, UPDRS part III, each UPDRS score, PD Questionnaire-39 (PDQ-39), and the modified Hoehn and Yahr stage at these same time-points, as well as the duration until the protocol is finished because additional levodopa is required or until the disease progresses, will also be analyzed. Adverse events and screening laboratory studies will also be examined. Participants in the hydrogen water group will drink 1000 mL/day of H_2_ water, and those in the placebo water group will drink normal water. One-hundred-and-seventy-eight participants with PD (89 women, 89 men; mean age: 64.2 [SD 9.2] years, total UPDRS: 23.7 [11.8], with levodopa medication: 154 participants, without levodopa medication: 24 participants; daily levodopa dose: 344.1 [202.8] mg, total levodopa equivalent dose: 592.0 [317.6] mg) were enrolled in 14 hospitals and were randomized.

**Discussion:**

This study will confirm whether H_2_ water can improve PD symptoms.

**Trial registration:**

UMIN000010014 (February, 13, 2013)

## Background

In patients with Parkinson’s disease (PD), the pharmacologic replacement of dopamine and other antiparkinsonian drugs has been used for symptomatic therapy. However, none of these drugs stop or lessen the dopaminergic neuronal degeneration or the progression of the disease. Findings of increased iron and lipid peroxidation and decreased levels of reduced glutathione in the substantia nigra strongly suggest that enhanced oxidative stress is involved in the pathogenesis of PD [1, 2]. Thus, antioxidant therapies might slow the progression of PD. Molecular hydrogen (H_2_) has recently been highlighted as a therapeutic and preventive antioxidant. Since the first publication [3], more than 150 papers have confirmed the efficacy of H_2_ in various animal models [4]. H_2_-water reduced dopaminergic neuronal cell loss in a 1-methyl-4-phenyl-1,2,3,6-tetrahydropyridine (MPTP) mouse model [5] as well as 6-hydroxydopamine did [6]. Our previous randomized double-blind study has shown that drinking 1,000 mL of H_2_-water for 48 weeks significantly improved (*p* < 0.05) the total Unified Parkinson’s Disease Rating Scale (UPDRS) scores of patients with PD who were being treated with levodopa [7]. In the present study, we aimed to confirm these results by conducting a longer and more large-scale trial that also included patients who were not being treated with levodopa. Here, we present the design and the baseline characteristics of participants already enrolled in this study.

## Methods

A placebo-controlled, randomized, double-blind, parallel-group (1:1) clinical multi-center trial was organized by the Department of Neurology of Juntendo University School of Medicine in accordance with Consolidated Standards of Reporting Trials (CONSORT) guideline. Fourteen hospitals are involved as trial centers. This trial was advertised in posters and on homepages of our clinic, and participants had to declare their intentions to participate voluntarily. The inclusion criteria required that the participants have a diagnosis of PD according to the United Kingdom Brain Bank criteria [8]. All the participants should have a modified Hoehn and Yahr staging (H & Y stage) in the on-phase between 1 and 4. For 8 weeks prior to establishing the baseline, the participants’ antiparkinsonian drugs were not changed. None of the participants have dementia (MMSE < 25) or dysphagia for water. Outpatients are preferred over admitted patients. The participants are to be older than 20 years. The exclusion criteria included the following: parkinsonism due to diseases other than PD, the presence of other serious diseases, malignant tumor(s), or adverse events caused by drugs.

The clinical study is registered at UMIN clinical trial registry (UMIN-CTR) UMIN000010014 (February 13, 2013). The Ethics Committee of the Juntendo University School of Medicine approved this study in February 2013, as did the ethics committees of other centers, and all participants provided signed informed consent forms.

### Randomization and blinding

The enrolled participants have been assigned using a stratified randomization method according to their age and if they were receiving levodopa. The assignments were made by [name] The participants and those assessing outcomes will remain blinded until all the participants have finished the protocol.

### Procedures

On a daily basis, the participants will drink 1,000 mL of saturated H_2_-water containing 5 mM of dissolved H_2_ (using Hydrogen 7.0, supplied by Ecomo International Co., Ltd. [Fukuoka, Japan]; patent No: PCT/JP2011/063601) for 72 weeks. The placebo water is saturated with N_2_. The water is contained in a 500-mL plastic bottle, and the participants will drink 2 bottles per day. The participants will drink the water within 3 h of opening the cap, because H_2_ evaporates. The bottles of H_2_-water or placebo water will be sent to the participants’ home every week.

The schedule of the study is shown in Fig. 1. Changes in the total UPDRS scores from baseline to the 8^th^, 24^th^, 48^th^, and 72^nd^ weeks, and after the 8^th^ week, are evaluated. The primary endpoint of the efficacy of this treatment in PD is the change in the total UPDRS score from baseline to the 72^nd^ week.

**Fig. 1 Fig1:**
[figure not shown]
Schedule of enrolment, intervention, and assessment. Study period of enrolment, allocation, and baseline may coincide. It is approximately 1 week to 10 days from allocation to the first day to start shipping the water. *1: Unified Parkinson’s Disease Rating Scale. *2: Parkinson’s Disease Questionnaire-39

The changes in UPDRS part II, UPDRS part III, each UPDRS score, PD Questionnaire-39 (PDQ-39), and the H & Y stage at these same time-points, as well as the duration until the protocol is finished because additional levodopa is required or until the disease progresses, will also be analyzed. Adverse events and screening laboratory parameters (total protein, albumin, alkaline phosphatase, aspartate transaminase, alanine transaminase, serum urea nitrogen, calcium, chloride, creatinine, glucose, lactate dehydrogenase, potassium, sodium, creatinine kinase, uric acid, choline esterase, LDL-cholesterol, HDL-cholesterol, and triglyceride levels) will also be examined.

### Statistical analysis

We calculated that a minimum of 95.4 participants need to be enrolled to detect a 5-point difference in the UPDRS scores between the 2 groups, with a standard deviation of the mean difference of 10, and a 2-sided alpha level of 0.05 and 80 %. Assuming a 35 % dropout, 96 participants will be required in total. A period of 72 weeks’ follow-up is a relatively long-term clinical trial in PD; hence, we assumed a 35 % dropout rate.

Variations in the endpoints between the baseline value and treatment assessment points will be compared between the groups, using a *t*-test or a Mann–Whitney U-test. The statistical tests are 2-sided, and the significance level is set at 0.05. The number of participants in the treatment and placebo groups who drop out due to disease progression will be analyzed using Kaplan − Meier curves and the log-rank test. Subgroup analysis (sex, and treatment with or without levodopa) will be performed.

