### Enrollment and data collection

One-hundred-and-seventy-eight Japanese participants with PD have already been enrolled in 14 hospitals and have been randomized, between April 1, 2013 and September 30, 2015, at their baseline visit. The participants will be followed-up for 80 weeks. The baseline characteristics are shown in Table 1. Despite extensive efforts to enroll more participants, the expected number of participants was not met, as it is difficult for some patients to consume 1000 mL water daily.

**Table 1 Tab1:** The baseline characteristics of the study participants

	Mean	Std. Deviation
Age	64.2	9.2
Disease duration	6.8	4.5
Sex (male/female) n	89	89
Wearing off (+/-) n	58	120
Dyskinesia (+/-) n	42	136
Levodopa mg	344.1	202.8
Levodopa (+/-) n	154	24
Dopamine agonist levodopa equivalent dose (mg) [12]	166.3	121.1
Total levodopa equivalent dose (mg) [12]^a^	592.0	317.6
Unified Parkinson’s Disease Rating Scale		
Part I	0.7	1.2
Part II	5.6	3.9
Part III	15.7	8.4
Part IV	1.7	2.2
Total	23.7	11.8
Modified Hoehn and Yahr stage	2.1	0.6
Parkinson’s disease Questionnaire-39		
Mobility	10.4	9.1
Activities of daily living	5.2	5.1
Emotional well-being	6.0	4.4
Stigma	3.2	2.8
Social support	1.4	1.9
Cognitions	4.0	3.0
Communication	1.7	2.2
Body discomfort	2.5	2.6
Total	34.4	24.2

^a^: not including istradefylline and zonisamide

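### The stated total of 96 participants is about half what the sample-size inputs require (about 96 to 99 per group, 192 to 198 in total); at the 178 enrolled, power is about 76%, not 80%

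*Protocol article*

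**What the plan says.** The sample-size paragraph under Statistical analysis in the protocol article puts the requirement at "a minimum of 95.4 participants need to be enrolled to detect a 5-point difference in the UPDRS scores between the 2 groups". For the variability it uses the phrase "with a standard deviation of the mean difference of 10". The significance level is two-sided 0.05, followed by a bare figure of 80%. The word 'power' is missing, but 80% can only be the power. After allowing for 35% dropout, the paragraph concludes that "96 participants will be required in total". The same section names a t-test or Mann–Whitney U-test for the between-group comparison of changes. The opening of Methods gives 1:1 allocation.

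The section Enrollment and data collection reports 178 participants randomised between April 2013 and September 2015, and states that despite recruitment efforts "the expected number of participants was not met".

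**The concern.** Three things do not fit together.

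- **The total is too small for its inputs.** A standardised difference of 5/10 = 0.5 at 80% power needs more than 120 evaluable participants before any dropout allowance. A total of 96 including 35% dropout cannot supply them.
- **The dropout step does nothing.** The text moves from 95.4 to 96 when it applies a 35% allowance. That is rounding up, not inflation; inflating 95.4 for 35% dropout would give 95.4/0.65 = 146.8, so 147.
- **The enrolment section contradicts the target.** An enrolment of 178 is 178/96 = 1.85 times 96, yet the target is reported as missed.

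At stake is how the primary result will be read. On the printed target the trial looks generously overpowered, and a null result on the week-72 change in total UPDRS would look firmer than it is. On its own assumptions the trial fell short of its target and of its nominal 80% power.

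**Working it through.** **Inputs**, all from Statistical analysis except the allocation ratio (Methods, opening paragraph): difference δ = 5; SD σ = 10, read as the SD of the change score within each arm; two-sided α = 0.05; power 80%; dropout 35%; allocation 1:1; two-sample t-test.

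**1. Reproducing the printed figure.**

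Normal formula, per group: n = 2 × (1.960 + 0.8416)² × (10/5)² = 62.8.

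- 62/0.65 = 95.38, which matches the printed 95.4 and rounds up to 96.
- 62.8/0.65 = 96.6, so 97.

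With σ = 10 in each arm, the printed 95.4 is therefore a per-group number with the dropout already in it. That 62.8 was cut to 62 is an inference, but it is the value that gives 95.4.

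**2. What the inputs require.**

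| Method | Evaluable per group | After 35% dropout, per group | Total |
|---|---|---|---|
| Value implied by 95.4 | 62 | 96 | 192 |
| Normal formula | 63 | 63/0.65 = 96.9, so 97 | 194 |
| t-test (noncentral t: 63.8) | 64 | 64/0.65 = 98.5, so 99 | 198 |

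**3. Other routes to 96 in total.**

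- One-sided α gives 50 per group, 100 before dropout and 154 after.
- Inflating by 1 + 0.35 instead of dividing by 0.65 gives 62.8 × 1.35 = 84.8 per group, or about 170 in total.

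Neither gives 96.

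**4. Power for the t-test** (noncentral t, effect size 0.5, 35% dropout).

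| Randomised in total | Evaluable per group | Power |
|---|---|---|
| 96 | 31.2 | 49% |
| 178 | 57.85 | 76% |
| 192 | 62.4 | 79% |
| 198 | 64.35 | 80% |

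With no dropout at all, 96 in total (48 per group) would still give only 68%.

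**5. Detectable difference at 178.** Scaling from the 63.8 per group that detect 5 points: 5 × √(63.8/57.85) = 5.25 points at 80% power.

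**6. Sensitivity of the 178 figure to dropout.** Power is 76% at 35% dropout, 79% at 30%, 82% at 25%, 84% at 20% and 91% at 0%.

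**The case against.** The strongest defence takes the wording about the SD literally. If 10 is the SD of a difference between two participants, the SD within each arm is 10/√2 = 7.07. The normal formula then gives 31.4 per group, or 62.8 in total, so 62/0.65 = 95.4 comes out as a total. Under that reading 96 in total has about 78% power after 35% dropout, and 178 has about 96%. The arithmetic alone therefore does not prove that 95.4 is a per-group number.

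That caution stands, but the reading does not survive the rest of the article. With a target of 96, an enrolment of 178 could not be described as falling short. It is also an unusual input for a parallel-group t-test, and the baseline SD of total UPDRS in Table 1 (11.8) sits more naturally with a within-arm SD near 10.

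Three smaller objections have some force:

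- The enrolment section gives no number. It shows only that the expected enrolment exceeded 178; about 192 is a reconstruction.
- No trial of 96 was run, so the 49% describes the printed target and not the trial. The actual loss at 178 is about 4 percentage points, and only if dropout reaches the assumed 35%.
- The underlying calculation was probably close to right, with the error in calling a per-group number a total.

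None of these makes the printed statement correct.

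**Conclusion.** The concern holds. Under the article's own inputs, with 10 as the SD of the individual change, the required total is 192 to 198, about twice the 96 stated. The printed target would give about 49% power after 35% dropout. The 178 enrolled give about 76%, with a detectable difference of 5.25 points. These power figures rest on a 5-point effect, SD 10, the unadjusted t-test and the full 35% dropout; at 25% dropout or less, 178 would exceed 80%.

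This is not detail left to a fuller document. The article states a wrong total and contradicts it in its next section. The practical shortfall at 178 is modest, but the printed target turns a shortfall into an apparent surplus.

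**What to change.** Replace the sample-size sentences with wording such as:

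> A total of 64 evaluable participants per group (128 in total) gives 80% power, at a two-sided significance level of 0.05, to detect a 5-point difference in the change in total UPDRS, assuming that the SD of the individual change is 10. Allowing for 35% dropout, 99 per group (198 in total) are required.

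Then add to the enrolment section:

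> A total of 178 participants were randomised. With 35% dropout about 116 would be evaluable, giving about 76% power for the unadjusted t-test (detectable difference 5.25 points at 80% power).

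The sponsor should check the original calculation and its definition of the SD. If the plan was 96 per group, the record should say so (192 in total, about 79% power by t-test) next to the recomputed requirement, so that the historical target is not overwritten.

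The cost is a text correction and a slightly less favourable power statement. Recruitment, endpoint, test and significance level are unchanged.

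### The two-sample test of week-72 UPDRS change does not allow for participants who stop because they worsen, so the primary comparison may be biased, probably towards no effect if hydrogen water works

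*Protocol article*

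**What the plan says.** Four statements in the protocol article bear on this.

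- **Endpoint (Methods, Procedures):** "The primary endpoint of the efficacy of this treatment in PD is the change in the total UPDRS score from baseline to the 72" (the 72nd week). UPDRS changes at weeks 8, 24 and 48 are also evaluated.
- **Test (Methods, Statistical analysis):** "Variations in the endpoints between the baseline value and treatment assessment points will be compared between the groups", with a t-test or a Mann–Whitney U-test.
- **End of participation (text under Fig. 1):** among the further outcomes is "the duration until the protocol is finished because additional levodopa is required or until the disease progresses". Needing more levodopa or progressing thus ends the protocol for that person.
- **Handling of progression (Statistical analysis):** "The number of participants in the treatment and placebo groups who drop out due to disease progression will be analyzed" by Kaplan–Meier curves and the log-rank test, apart from the primary comparison.

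The sample size is set "to detect a 5-point difference in the UPDRS scores between the 2 groups", "with a standard deviation of the mean difference of 10", at "a 2-sided alpha level of 0.05 and 80" per cent (power is plainly meant), with 35% dropout. The only reason given for 35% is the length of follow-up. It is not split by cause or arm.

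**The concern.** One way of leaving the trial is to get worse, and worsening is what the primary endpoint measures. A participant who stops at, say, week 30 for progression has no on-protocol week-72 score, and that absence carries information about the score. A single-visit two-sample test has no means of using it: the worsening recorded at earlier visits goes into other comparisons, and the stopping itself goes into the log-rank test.

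At stake are both the estimate and the power. If the treatment slows worsening and the same stopping criteria apply in both arms, placebo loses more of its worst cases. The remaining groups then look more alike than the randomised groups would. The planned dropout allowance replaces lost numbers but not the lost comparability.

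**Working it through.** **Inputs from the article:** difference 5; SD 10 (read as the SD of individual change); two-sided alpha 0.05; power 80%; dropout 35%; 178 randomised 1:1. I assume 89 per arm, because the split is not given.

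**Step 1: the plan's own figure.** Per arm, n = 2σ²(1.960 + 0.842)²/δ² = 2 × 100 × 7.849/25 = 62.8. Then 62/0.65 = 95.4, the stated figure (63/0.65 = 96.9). It reproduces as a number per arm, although the article labels 96 a total; that labelling is a separate point. What matters here is the 1/(1 − 0.35) inflation: planning assumes that those who drop out add nothing to the primary test and that their loss is harmless.

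**Step 2: power if loss is unrelated to outcome.** 89 × 0.65 = 57.85 per arm. SE = 10 × √(2/57.85) = 1.859. Power = Φ(5/1.859 − 1.96) = Φ(0.729) = 77%.

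**Step 3: loss partly driven by worsening.** Everything in this step is assumed, because the article gives no threshold and no split of the 35%.

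- Week-72 change is normal with SD 10, and the mean is 5 points higher (worse) on placebo.
- A stopping trigger has the same means and SD, and correlates ρ with week-72 change.
- A participant stops when the trigger exceeds c, the same c in both arms.
- A quarter, half or all of the 35% arises this way; the rest is random.

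With a = (c − mean)/10 and λ(a) = φ(a)/Φ(a), the completer mean in an arm is mean − 10ρλ(a). Hence

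completer difference = 5 − 10ρ(λ_placebo − λ_hydrogen).

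| Share of loss due to worsening | c | Total loss, placebo / hydrogen | λ_placebo, λ_hydrogen | Difference at ρ = 1.0 / 0.7 / 0.4 | Power, 89 per arm |
|---|---|---|---|---|---|
| All | 6.48 | 44% / 26% | 0.706, 0.436 | 2.30 / 3.11 / 3.92 | 44% / 49% / 59% |
| Half | 12.14 | 40% / 30% | 0.406, 0.215 | 3.10 / 3.67 / 4.24 | 56% / 59% / 65% |
| Quarter | 16.49 | 38% / 32% | 0.236, 0.108 | 3.72 / 4.10 / 4.49 | 64% / 66% / 69% |

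The completer variance is 100[1 − ρ²(aλ + λ²)]. In the first cell the SDs are 6.30 and 7.26, with 49.7 and 66.0 completers. SE = √(6.30²/49.7 + 7.26²/66.0) = 1.264, and power = Φ(2.30/1.264 − 1.96) = Φ(−0.140) = 44%.

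**Step 4: does the direction hold?** Now fix the loss in each arm, make all of it outcome-related, and take ρ = 0.7. λ is 0.497, 0.570 and 0.644 at 30%, 35% and 40% loss.

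- 40% placebo, 30% hydrogen: 5 − 7 × (0.644 − 0.497) = 3.97.
- 35% in each: 5 − 7 × 0 = 5.00.
- 30% placebo, 40% hydrogen: 5 − 7 × (0.497 − 0.644) = 6.03.

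Sign and size therefore depend on how loss differs between the arms.

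**The case against.** The strongest reply is that the article does not state a completer analysis. It names a test but no analysis set and no rule for a missing week-72 value. A t-test or Mann–Whitney test can be run on last-observed, imputed or rank-assigned values, and a full protocol or analysis plan may settle this. Inflating by 1/(1 − 0.35) is routine planning and does not fix who is analysed. This stands: a reader might infer that the test can use only those who reach week 72, but the sample size suggests that reading without confirming it. The missing rule is not the finding. The finding is that the stated test does not in itself deal with exits the article itself links to worsening.

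Two further inferences are tempting and unsupported. One is that the 35% lost are selected on outcome. The figure is all-cause, and the article mentions a burden unrelated to worsening, the daily water volume, though as an obstacle to enrolment. The other is that the effect will be attenuated; Step 4 shows that this needs more loss on placebo.

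It can also be said that the log-rank analysis and the comparisons at weeks 8, 24 and 48 would expose differential exit. They would, so a null primary result would not be uninterpretable. But they sit beside the primary estimate and do not correct it.

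Finally, a simulation in which exit depends only on recorded scores would show a repeated-measures model recovering the true difference. That follows from its construction, so I do not offer it as proof.

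**Conclusion.** The concern holds in conditional form. Stopping for added levodopa or progression is likely to make week-72 change informatively missing for part of those lost, and the stated test makes no correction. A comparison of observed week-72 changes may be biased. Under the trial's own hypothesis, with stopping criteria common to both arms, the expected direction is towards no effect.

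Over the assumed range, the shortfall from the true 5 points runs from about 10% to 54% (5 to 4.49, and 5 to 2.30), and 8 to 33 percentage points of power are lost from the 77% baseline. These sizes rest on a common threshold, normal changes, the assumed share of outcome-related loss, and 89 per arm. They illustrate the risk and do not predict this trial's result.

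**What to change.** Before unblinding, replace the week-72 two-sample test as primary analysis with a mixed model for repeated measures on change in total UPDRS at weeks 8, 24, 48 and 72:

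- all randomised participants with at least one post-baseline score;
- terms for treatment, visit, treatment-by-visit, baseline-by-visit, and the randomisation strata (age and levodopa use);
- unstructured covariance;
- the week-72 treatment contrast as the primary result.

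Add a sensitivity analysis that ranks participants who stopped for progression or added levodopa worst and compares the arms on ranks. State how participants lost for other reasons enter that ranking.

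The cost is a change of analysis wording. The scores at weeks 8, 24 and 48 are already planned, and the section on randomization and blinding keeps participants and assessors blinded until everyone has finished. The price is reliance on missing at random: given the scores already recorded, stopping must carry no further information about later ones. The worst-rank analysis shows whether the conclusion depends on that assumption, although it answers a somewhat different question because it counts stopping for worsening as the outcome. Participants with no post-baseline score remain outside the model, and their number by arm should be reported.

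### The primary comparison of UPDRS change is unadjusted: it uses neither baseline UPDRS nor the randomisation strata, giving up precision that data already held could supply

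*Protocol article*

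**What the plan says.** The Procedures section makes the week-72 change in total UPDRS the primary efficacy endpoint. The Statistical analysis section states: "Variations in the endpoints between the baseline value and treatment assessment points will be compared between the groups". The tests it names are the t-test and the Mann–Whitney U-test. It mentions no covariate and no stratification term.

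Under Randomization and blinding, participants were "assigned using a stratified randomization method according to their age and if they were receiving levodopa". Levodopa use comes back in the analysis only as a subgroup factor, and age does not come back at all.

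Table 1 shows that baseline total UPDRS has been recorded (mean 23.7, SD 11.8). It also shows 154 participants on levodopa and 24 not.

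The sample size was set "to detect a 5-point difference in the UPDRS scores between the 2 groups". Variability enters the calculation as follows: "with a standard deviation of the mean difference of 10". The error rates are given as "a 2-sided alpha level of 0.05 and 80" per cent, the last figure being read here as power. The result is stated thus: "Assuming a 35 % dropout, 96 participants will be required in total". The Enrollment and data collection section reports 178 randomised and says that the expected number was not reached.

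**The concern.** A comparison of raw change gives baseline a fixed weight of one. If the slope of week-72 score on baseline is below one, change scores over-correct: an arm that starts higher by chance will tend to show a more favourable change for that reason alone. The direction is unknown in advance, so the cost is added noise in the estimate. Separately, if age or levodopa use predicts the outcome, balancing on it at randomisation and then leaving it out of the analysis makes the standard error larger than it need be.

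The stake is precision. Recruitment is closed and 35% dropout is expected, so a more efficient analysis is one of the few ways left to gain power. The article names its test, so this is a stated choice and not a detail left for a later document.

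**Working it through.** **Inputs from the article.** Difference 5; SD 10, read as the SD of individual change; two-sided alpha 0.05; 80% power; 35% dropout; 178 randomised 1:1; baseline SD 11.8.

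**Input not in the article.** The week-72 SD, written s. The main case assumes s = 11.8; a range follows.

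**The plan's own figure.** The normal formula gives 2 × (10 × (1.96 + 0.842)/5)² = 62.8 per arm. Allowing for dropout, 62/0.65 = 95.4 and 62.8/0.65 = 96.6. The stated 95.4, rounded to 96, is therefore reproduced as a per-arm number, which makes the target 192. This supports reading the SD of 10 as that of individual change. Read as a total, 96 would give only about 68% power even without dropout, and 178 enrolled would exceed the target, contrary to the statement that the expected number was missed.

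**Unadjusted power (noncentral t, SD 10).**
- 192 enrolled: 192 × 0.65/2 = 62.4 per arm, power 79.1%.
- 178 enrolled: 178 × 0.65/2 = 57.85 per arm, power 76.0%.
- Cost of the shortfall on the per-arm reading: 3.1 points.

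**ANCOVA on baseline.**
- Covariance of baseline and change = (s² − 11.8² − 10²)/2.
- r = covariance/(11.8 × 10).
- Residual variance = 100 × (1 − r²).

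At s = 11.8 the covariance is −50 and r = −50/118 = −0.424. The variance ratio is 1 − 0.180 = 0.820 and the residual SD is 9.06. The implied correlation between baseline and week 72 is 1 − 100/(2 × 11.8²) = 0.64. Power is 83.7%, a gain of 7.7 points, equivalent to enrolling 178/0.820 = 217.

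**Range, with change SD held at 10 and 57.85 per arm.**

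| Week-72 SD | Variance ratio | Residual SD | Power |
|---|---|---|---|
| 10 | 0.652 | 8.07 | 91.0% |
| 11.8 | 0.820 | 9.06 | 83.7% |
| 13 | 0.911 | 9.55 | 79.8% |
| 13.25 | 0.927 | 9.63 | 79.1% |
| 14 | 0.966 | 9.83 | 77.4% |
| 15 | 0.996 | 9.98 | 76.2% |
| 15.47 | 1.000 | 10.00 | 76.0% |
| 17 | 0.956 | 9.78 | 77.9% |

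**Break-even with the shortfall.** Matching 192 enrolled needs a variance ratio of at most 178/192 = 0.927, reached at s of about 13.25 (12% above the baseline SD). The gain is nil where s² = 11.8² + 10², that is s = 15.47, and slowly returns above that. If the two SDs are equal but the correlation differs from 0.64, the variance ratio is (1 + correlation)/2, and break-even falls at a correlation of about 0.85.

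**Chance imbalance, at s = 11.8.** The standard error of the baseline difference between arms is 11.8 × √(2/57.85) = 2.19 points. The slope of change on baseline is −(1 − 0.64) = −0.36, so an imbalance of one standard error moves the unadjusted estimate by about 0.36 × 2.19 = 0.79 points, and two standard errors by about 1.6, against a target of 5.

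**Strata.** The article gives nothing on how strongly age or levodopa use predicts change, so no gain is credited to them.

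**The case against.** A two-sample test of change is a legitimate primary analysis in a randomised trial. Regression to the mean acts equally on both arms in expectation, so the contrast is unbiased, and ignoring prognostic strata makes the test conservative without inflating type I error. A reader might infer that the planned test is invalid or that an imbalance has already occurred. The document supports neither: Table 1 is not split by arm.

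A reader might also infer that ANCOVA would certainly recover more power than the recruitment shortfall cost. That is conditional in two ways. The shortfall has a size only if 96 is taken as per arm, which fits the arithmetic and the enrolment statement but contradicts the printed text. And the recovery exceeds the cost only up to a week-72 SD of about 13.2; at 14 the gain is 1.4 points against a cost of 3.1. Scores could well spread out that much over 72 weeks of a progressive disease.

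Nor can an extra gain from age and levodopa use be claimed. Only 24 of 178 participants are without levodopa, and either factor may add little once baseline is in the model.

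Finally, covariate terms are often left to an analysis plan, which is not shown here. That defence is weak, because the article names a specific unadjusted test.

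These objections limit the size and seriousness of the point. They do not remove it: in large samples ANCOVA is no less efficient than the change-score test, and the covariates are already in hand.

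**Conclusion.** The point holds as one of efficiency, not validity. The stated test leaves out baseline UPDRS and both stratification factors. Adjusting for baseline would raise power from about 76% to 84%, provided that the SD of 10 is that of individual change, dropout is 35% and the week-72 SD equals the baseline SD. Over week-72 SDs from 10 to 15.5, the adjusted power runs from about 91% down to 76%, the latter being no gain. If the target was 192, adjustment offsets the roughly 3-point cost of stopping at 178 only when the week-72 SD is at most about 13.2. The contribution of the strata is unknown. This is a free improvement that should be made; it does not undermine the trial.

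**What to change.** Before unblinding, specify the primary analysis as an ANCOVA of change in total UPDRS at week 72, or the week-72 contrast of a repeated-measures model, with baseline total UPDRS, age stratum and levodopa use (yes/no) as covariates. Report the adjusted difference with its 95% CI. Keep the unadjusted t-test as a sensitivity analysis. Naming one model also settles the open choice between a t-test and a Mann–Whitney U-test for the primary endpoint.

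The cost is a change of analysis wording. No new data, visits or participants are needed.

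### The primary week-72 UPDRS comparison is left to one of two unadjusted tests without saying which, although the trial is sized on a difference in means

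*Protocol article*

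**What the plan says.** Three statements in the protocol article bear on the primary comparison.

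- **Endpoint.** Under Procedures, the primary efficacy endpoint "is the change in the total UPDRS score from baseline to the 72^nd^ week". Variable and time point are therefore fixed.
- **Test.** Under Statistical analysis, "Variations in the endpoints between the baseline value and treatment assessment points will be compared between the groups", "using a *t*-test or a Mann–Whitney U-test". One sentence serves all change endpoints at all visits: total UPDRS, its parts, PDQ-39 and the modified Hoehn and Yahr stage. The next sentence adds: "The statistical tests are 2-sided, and the significance level is set at 0.05". Neither test uses the baseline score as a covariate or the stratification factors.
- **Sample size.** The same section plans "to detect a 5-point difference in the UPDRS scores between the 2 groups", "with a standard deviation of the mean difference of 10", at "a 2-sided alpha level of 0.05 and 80" % (evidently power).

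Under Randomization and blinding, assignment is stratified by age and levodopa use. The same paragraph says that participants and outcome assessors "will remain blinded until all the participants have finished the protocol".

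**The concern.** The t-test compares means. The Mann–Whitney test compares rank ordering and gives no estimate of the 5-point difference for which the trial was planned. The two can disagree on the same data. A trial meant to confirm an earlier result needs one primary analysis, so that a result near 0.05 cannot depend on which test was reported. As printed, the article leaves two candidates for the primary endpoint and gives no rule for deciding between them.

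Both candidates are also unadjusted, although baseline total UPDRS is recorded for everyone and the randomisation was stratified. The choice therefore concerns the summary measure (mean difference or rank ordering) and, to a smaller degree, precision.

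**Working it through.** **Inputs.** From the article: difference 5, SD 10, two-sided 0.05, 80%, dropout 35%, allocation 1:1, 178 randomised. Assumed: an equal split of 89 per arm, dropout exactly as planned, 10 read as the per-participant SD of the change, and the distribution shapes below. The article gives no shape for the UPDRS change.

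**1. The plan's own figure.** For two means, n per arm = 2 × [SD × (1.960 + 0.842) / difference]² = 2 × (10 × 2.802 / 5)² = 62.8, so 63. The article's 95.4 equals 62 / 0.65 = 95.38. It is thus a comparison of two means inflated for 35% dropout, and it reproduces as a per-group number. That the article prints it as a total is a separate matter. What matters here is that the calculation is built on means.

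**2. Expected completers.** 178 / 2 = 89 per arm; 89 × 0.65 = 57.9, about 58 per arm.

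**3. Type I error at 58 per arm.** Null trials were simulated (100,000 per shape, except where noted), both tests at two-sided 0.05.

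| Shape | t-test alone | Mann–Whitney alone | Smaller p-value taken |
|---|---|---|---|
| Normal | 5.0% | 4.9% | 5.9% |
| t, 5 df (8,000 trials) | 5.0–5.2% | 5.0–5.2% | 6.5% |
| Gamma, shape 2 | 4.9% | 5.0% | 6.6% |

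More extreme shapes give 6.7% (t, 3 df) and 7.3% (lognormal) in the last column. If a Shapiro–Wilk pre-test picks the test, the level is 4.8–5.2% (10,000 trials; normal, gamma and t with 3 df).

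**4. How often the choice matters.** At the planned effect of 5/10 = 0.5 SD, the two tests disagree on significance in about 6% of trials with normal data, 10% with t (5 df) and 13% with gamma.

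**5. What adjustment buys.** Power ≈ Φ(5 / [SD × √(2/58)] − 1.960), with √(2/58) = 0.1857. If baseline and change correlate at r in size, the residual SD is 10 × √(1 − r²).

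- Unadjusted: 5 / 1.857 = 2.693; Φ(0.733) = 77%.
- r = 0.3: SD 9.54; 5 / 1.771 = 2.823; Φ(0.863) = 81%.
- r = 0.5: SD 8.66; 5 / 1.608 = 3.109; Φ(1.149) = 87%.

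The range for r is an assumption; the article reports no such correlation. At r = 0 the model loses only a few degrees of freedom.

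**The case against.** The test sentence covers a mix of endpoints, one of them an ordinal stage, so the word joining the two tests may mean a choice by type of variable. The sample size, built on a mean and an SD, is evidence that the t-test was intended for the primary endpoint. The article condenses a fuller protocol, and a statistical analysis plan not shown may hold the rule. On this view the point is at most a request for clarification.

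Part of this stands. The intended test can be guessed, and it may be fixed elsewhere. But the article does speak to the primary test, and it names two. Nothing in the section states a split by type of variable.

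A reader might infer three stronger things, and the document supports none of them.

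- **That the 5% level is not held.** Each test alone holds it, and so does a normality pre-test. The excess needs both tests to be run with results in view and the better one reported, which the article nowhere plans.
- **That the blinding rule is deficient.** Keeping participants and assessors blinded to the end of follow-up is usual and protects outcome assessment. Silence on analyst blinding and database lock is what an article leaves to the full protocol.
- **That the whole estimand is open.** Variable, time point and treatment groups are stated. Only the summary measure is not.

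It can also be said that an adjusted model replaces both named tests and so goes beyond choosing one. That is true. It is proposed because it estimates the planned mean difference, respects the stratified randomisation and needs no new data. Naming the unadjusted t-test alone would also remove the ambiguity.

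**Conclusion.** The point holds in a limited form. The article does not say which of two unadjusted tests is primary for the week-72 change in total UPDRS, while its sample size presupposes a difference in means. The potential inflation is about 1 to 2 percentage points (about 6 to 7% against 5%), and only if the choice follows the results. That size rests on 58 completers per arm and on the assumed normal, t with 5 df and gamma shapes. The weakness should be corrected, but it is not fatal to the trial. The gain from adjustment, from about 77% to about 81–87% power, depends on the assumed correlation of 0.3 to 0.5 and on reading 10 as the per-participant SD.

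**What to change.** Before unblinding, state one primary analysis: the between-group mean difference in the change in total UPDRS from baseline to week 72, with 95% confidence interval, from a linear model adjusted for baseline total UPDRS and the randomisation strata (age and levodopa use), tested two-sided at 0.05. At about 58 per arm no normality pre-test is needed. List the Mann–Whitney test as a sensitivity analysis that cannot replace the primary result. Say separately which test applies to each secondary endpoint; a rank method suits the modified Hoehn and Yahr stage.

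The cost is one or two sentences in the analysis plan. No visit, participant or data item changes, because baseline UPDRS and the stratification factors are already recorded. If a full analysis plan already fixes the primary test, citing it and its date is enough to settle which test is primary.
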